## PSMA PET/CT IMAGING

PSMA PET/CT scans as part of the study will be performed with [^68^Ga]Ga-PSMA-11 (injected activity 185 MBq [range, 111–259 MBq], uptake time 50–100 min) with intravenous CT contrast. For more details, see section 6.8 of the study protocol in the supplemental materials.

## ^177^LU-PSMA SPECT/CT IMAGING

Patients will be imaged with posttreatment quantitative SPECT/CT scans at more than 24 h after administration of [^177^Lu]Lu-PSMA-617 (allowed time window for image acquisition, 24–72 h). SPECT/CT scan coverage will extend from midthigh to the vertex with 3 bed positions (∼18 min per bed position, 120 views per bed, 15 s per view). Dosimetry will be performed using MIM software. For more details, see section 6.9 of the study protocol in the supplemental materials.

## STUDY DURATION

Patients may be treated for up to 12 cycles (investigational arm) or 6 cycles (control arm) of [^177^Lu]Lu-PSMA-617 therapy until progressive disease (except for progression during treatment holiday periods in the investigational arm which will lead to treatment continuation), withdrawal of consent, the occurrence of unacceptable toxicity, or a determination by the investigator if the patient is not clinically benefiting.

The duration of subject participation will be from the time of signing informed consent through the 24-mo postinjection visit. The planned duration for the whole study is 48 mo. The study enrollment started in August 2024. Trial completion date is anticipated for December 2028.

## STATISTICS AND SAMPLE SIZE DETERMINATION

The primary endpoint of the study is the 2-y survival rate from the date of the first cycle of [^177^Lu]Lu-PSMA-617 therapy. We assumed that the 2-y survival rate in the control group would be 30%. We hypothesized that the 2-y survival rate in the investigational group would be 55%. A 2-sided log-rank test with an overall sample size of 90 subjects (45 in the control group and 45 in the treatment group) achieves 80.3% power at a 0.05 significance level to detect a hazard ratio of 0.50 when the proportion surviving in the control group is 0.30 and the proportion surviving in the treatment group is 0.55 at 24 mo. The study lasts for 48 mo, of which subject accrual (entry) occurs in the first 12 mo.

The accrual pattern across months is uniform (all periods equal). The proportion dropping out or lost to follow-up in the control group and treatment groups is assumed to be around 6 per group during the study period.

This calculation was performed using power analysis and sample size, and the 2-y survival estimates used in the calculation were estimated from the VISION trial data (2).

Randomization is centrally performed in a 1:1 ratio to the 2 treatment arms. The clinical investigators are blinded to the randomization sequence that has been created upfront in collaboration with the local Department of Medicine Statistics using the software application REDCap (Research Electronic Data Capture) (16). On actual sequential allocation of a patient to a treatment arm, both the study team and the patient will be aware of the treatment arm (open label study).

Efficacy will be reported using descriptive statistics by means of number and percentage of patients dead 24 mo after the first cycle (2-y survival rate). Distribution of safety and tolerability results will be compared between both groups using appropriate tests (e.g., χ^2^ tests). Descriptive analyses (median, standard deviation) will be used to determine OS and PFS; group comparisons will be performed using appropriate tests including survival analyses (e.g., Kaplan–Meier estimator). For more details of the statistical analysis plan, see section 10 of the study protocol in the supplemental materials.

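### The 80.3% power assumes 36 to 48 months of follow-up, which conflicts with participation ending at the 24-month visit and with a 24-month endpoint

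*Protocol article*

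**What the plan says.** Under Statistics and Sample Size Determination, the article says that a two-sided log-rank test with 45 patients per arm "achieves 80.3% power at a 0.05 significance level to detect a hazard ratio of 0.50", where "the proportion surviving in the control group is 0.30 and the proportion surviving in the treatment group is 0.55 at 24 mo". The timeline behind this is "The study lasts for 48 mo, of which subject accrual (entry) occurs in the first 12 mo", with uniform entry. About six patients per group are assumed lost during the study period.

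Under Study Duration: "The duration of subject participation will be from the time of signing informed consent through the 24-mo postinjection visit". The injection that starts this clock is not named. The safety schedule under Investigational Arm Timeline also runs to a total of 24 months. The planned length of the whole study is 48 months.

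The primary endpoint is the 2-year survival rate from the first cycle, reported as the number and percentage dead at 24 months. Overall survival is a secondary endpoint, counted from the first cycle to death with no stated cut-off.

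**The concern.** The two sections imply different follow-up. With entry in the first 12 of 48 months, the power calculation gives each patient 36 to 48 months of potential follow-up and counts deaths in that window. The participation rule gives 24 months, and the named endpoint uses nothing after month 24. Log-rank power depends on the number of deaths, so the later deaths matter: below they are about 15 of 65.

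The article says the trial was powered to show a survival benefit. If the later deaths are not collected or not used, the chance of missing the assumed effect is nearer 30% than 20%, and readers would judge a non-significant result against a power the trial did not have.

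**Working it through.** **Inputs from the article.** Two-sided alpha 0.05; 45 per arm; survival at 24 months 0.30 and 0.55; uniform entry over 12 months; total 48 months; about six lost per arm. **Assumptions.** Exponential survival and loss; the six read as 6 of 45 patients.

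**Hazards.** Control: −ln(0.30)/24 = 0.0502 per month. Investigational: −ln(0.55)/24 = 0.0249. Ratio 0.497, ln = −0.700. Loss, if spread over 48 months: η = −ln(1 − 6/45)/48 = 0.0030.

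**Formulas.** Expected deaths per arm = 45 × λ/(λ+η) × average of [1 − exp(−(λ+η)f)] over the follow-up times f. Power (Schoenfeld) = Φ(√D/2 × |ln HR| − 1.96), with D the total deaths.

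**Step 1: reproduce the stated figure.** With f uniform on 36–48 months, D = 37.8 + 27.7 = 65.5. Power = Φ(8.09/2 × 0.700 − 1.96) = Φ(0.87) = 80.9%, or 80.1% at a hazard ratio of exactly 0.50. Simulation gives 80.7%. The stated 80.3% is reproduced.

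**Step 2: stop follow-up 24 months after the first cycle.**

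| Loss assumption | Deaths | Schoenfeld | Simulation (20,000 runs) |
|---|---|---|---|
| None | 51.7 | 71.2% | 71.1% |
| 6/45 over 48 months | 50.2 | 69.9% | 69.1% |
| 6/45 over 24 months | 48.8 | 68.6% | 67.7% |

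On the middle row, 65.5 − 50.2 = 15.3 of the deaths in the stated design fall after month 24. About 65 deaths are needed for 80% power.

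**Step 3: stop follow-up 24 months after the last cycle.** At 6-week intervals the sixth cycle falls at week 30 (about 7 months) and the twelfth at week 66 (about 15 months). The longest follow-up is then about 31 months in the control arm and 39 in the investigational arm, without holidays. With 6/45 lost over 48 months, D = 34.3 + 26.5 = 60.8, giving 77.9% by Schoenfeld and 74.9% by simulation. Across the three loss assumptions the simulation gives 73.8–76.9% and Schoenfeld 76.3–79.5%. Schoenfeld is the optimistic one here: once no control patient is at risk, a death in the other arm adds nothing to the log-rank statistic. For the same reason, longer follow-up of the investigational arm through holidays would not recover the difference.

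**Step 4: illustration on the 2-year rate.** Power = Φ{(0.25√n − 1.96 × √(2 × 0.425 × 0.575)) / √(0.30 × 0.70 + 0.55 × 0.45)}, where 0.425 is the mean of 0.30 and 0.55.

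- n = 45: Φ((1.677 − 1.370)/0.676) = 67.5%.
- n = 43: Φ((1.639 − 1.370)/0.676) = 65.5%. At the Step 1 loss rate about two patients per arm are lost alive by month 24, which leaves 43.
- n = 39: Φ((1.561 − 1.370)/0.676) = 61.1%. This removes all six losses per arm before month 24.

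**The case against.** The strongest reply is that the full protocol, to which the article refers for the assessment schedule and analysis detail, may provide survival follow-up to study closure. Overall survival is defined to death without a 24-month limit, and the whole study lasts 48 months. If vital status is collected to month 48, the log-rank test keeps about 80% power. This stands as a limit on the claim. A reader might infer that deaths after month 24 will be absent from the data; the article does not establish that. It shows only that the participation period it states does not cover them. Even with longer collection, a log-rank test to month 48 is not a comparison of 2-year rates.

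Three other readings go too far:

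- **That 80.3% is a miscalculation.** It is not, as Step 1 shows. The fault lies between sections.
- **That the trial's power is 61–67%.** The article names a log-rank test for power and reports the 2-year rate descriptively. The two-proportion test is an illustration, and its 61% floor puts all losses before month 24, whereas the article places them across the study period.
- **That the calendar is a separate error of weight.** Twelve months of accrual plus 24 of participation make 36, not 48, and August 2024 to the anticipated December 2028 completion is about 52. Start-up, close-out and analysis could explain this. It is minor, but worth tidying in the same edit.

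The loss wording could also mean 6% rather than six patients. That does not rescue the figure: with no loss at all, the 24-month cap gives only about 71%.

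**Conclusion.** The concern holds as an inconsistency. The 80.3% belongs to a design with 36–48 months of follow-up, and neither reading of the stated participation period supplies it. The shortfall is about 9–12 points if the clock runs from the first injection, and about 2–5 points (75–78%) if it runs from the last. The wording does not settle which applies, so neither range should be quoted without its condition. These figures rest on the article's own effect, sample size and alpha, on exponential survival, and on 6 of 45 lost per arm. The caps of 31 and 39 months are assumed maxima; patients who stop treatment early would have less.

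**What to change.** Choose one; neither needs more patients.

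- **Keep the 24-month horizon.** Restate the power as about 68–71% for a log-rank test censored at 24 months or, if the 2-year proportions are to be compared, about 61–67%. The cost is a less favourable figure and acceptance of a type II error of about 30% or more. For scale, 80% on the censored log-rank test would take about 114–120 patients in total (65 deaths divided by a death probability of 0.575 to 0.542).
- **Follow vital status to a common closure.** Say so, run the log-rank test on overall survival at that point, name it as the primary analysis, and report the 2-year rate as an estimate. At the Step 1 loss rate, power is about 81% with 12-month accrual (65.5 deaths) and about 78% with 24-month accrual (61.0 deaths). The cost is a protocol change to the primary analysis plus vital-status checks on survivors.

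In either case, make accrual, follow-up and closure agree between Study Duration and Statistics and Sample Size Determination, and say whether postinjection refers to the first or the last injection.

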## STUDY DESIGN

### Overall Study Design

This is a prospective, open-label, randomized, controlled, parallel group, single-center phase 2 trial of a flexible and extended dosing schedule of [^177^Lu]Lu-PSMA-617 therapy in comparison to the standard fixed dosing schedule in patients with mCRPC.

The study was powered to demonstrate a survival benefit of the flexible and extended dosing schedule in comparison to the standard fixed dosing schedule. We hypothesized a 2-y survival rate of 55% in the investigational group and 30% in the control group (2). The overall sample size is 90 patients (45 in the control group and 45 in the treatment group) to achieve 80% power. The planned study duration is 48 mo.

The flexible dosing schedule in the investigational arm will be based on SPECT/CT response assessments obtained 24 h after the injection of [^177^Lu]Lu-PSMA-617. The response assessment during treatment holiday periods will be based on prostate-specific membrane antigen (PSMA) PET/CT every 12 wk using RECIP guidelines.

Single-time-point SPECT/CT dosimetry protocol at every cycle will be performed and will allow the number of cycles that subjects may receive under the study without exceeding the kidney dose threshold to be determined. An interim safety analysis with a stopping rule based on safety outcomes is planned at 50% of enrollment.

The overall study design is shown in Figure 1.

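### The stated primary result is a crude percentage dead at 24 months, which does not match the log-rank test behind the 80.3% power and has no place for patients lost to follow-up

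*Protocol article*

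**What the plan says.** All but one of the statements are in the Protocol article under Statistics and Sample Size Determination.

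- **Sizing.** The calculation is for a two-sided log-rank test with 45 patients per arm, 90 in all, which by the article's account "achieves 80.3% power at a 0.05 significance level to detect a hazard ratio of 0.50". The inputs are: "We assumed that the 2-y survival rate in the control group would be 30" per cent, and "We hypothesized that the 2-y survival rate in the investigational group would be 55" per cent. Accrual takes 12 months of a 48-month study.
- **Aim.** Under Overall Study Design: "The study was powered to demonstrate a survival benefit of the flexible and extended dosing schedule".
- **Loss.** The number lost "is assumed to be around 6 per group during the study period".
- **Primary reporting.** Efficacy is to be described by the "number and percentage of patients dead 24 mo after the first cycle (2-y survival rate").
- **OS and PFS.** "Descriptive analyses (median, standard deviation) will be used to determine OS and PFS". The same sentence goes on to plan group comparisons by suitable tests, including survival analyses, with the Kaplan–Meier estimator as its example.
- **Further detail** is referred to section 10 of the full protocol, which is not shown.

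**The concern.** The sizing paragraph and the analysis paragraph describe different analyses. The first rests on a log-rank comparison of survival times. The second reports a 24-month head count and attaches no test to it. The chi-square example belongs to safety, and the Kaplan–Meier example belongs to the OS and PFS sentence and is an estimator rather than a test.

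Three things follow if the text is applied as written:

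- The headline rate has no defined treatment of patients whose status at 24 months is unknown.
- If the reported proportions are what gets compared, the power is not the power claimed.
- The percentage dead carries the name of its complement. Nothing numerical changes, but a result table built from this text could be misread.

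In an open-label trial, the comparison that decides the primary endpoint should be fixed before outcomes are seen.

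**Working it through.** **Inputs.** From the Protocol article: 45 per arm; 24-month survival 0.30 and 0.55; two-sided 0.05; 12 months of uniform accrual in a 48-month study; about 6 lost per group, read as a count (6/45 = 13.3%). Assumed here: exponential death and dropout times, with dropout unrelated to prognosis.

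**1. Reproduce the stated power.**
- Monthly death rates: −ln(0.30)/24 = 0.0502 and −ln(0.55)/24 = 0.0249. Hazard ratio = 0.0249/0.0502 = 0.497, stated as 0.50.
- Dropout rate with 6/45 spread over 48 months: −ln(1 − 6/45)/48 = 0.00298 per month.
- Expected deaths when every patient is followed to month 48 (36 to 48 months each): 37.8 + 27.7 = 65.5.
- Schoenfeld: power = Φ(√D/2 × |ln HR| − 1.96). With D = 65.5 and HR 0.50: Φ(2.805 − 1.960) = 80.1%. With HR 0.497: 80.9%. A Lakatos-type calculation gives 79.9% and 80.6%.

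The stated 80.3% is reproduced, for a log-rank test with follow-up to month 48.

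**2. Power if the reported proportions are compared.**
- Pooled z, with pooled proportion (0.30 + 0.55)/2 = 0.425. Standard error under the null: √(2 × 0.425 × 0.575/45) = 0.1042. Under the alternative: √((0.30 × 0.70 + 0.55 × 0.45)/45) = 0.1008.
- Power = Φ((0.25 − 1.96 × 0.1042)/0.1008) = Φ(0.454) = 67.5%.
- Fisher's exact test by full enumeration: 59.0%.
- If the 6 lost per arm are dropped (39 per arm): 61.1% (z) and 52.9% (Fisher).
- For 80% power the z comparison needs 61 per arm before dropout.

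**3. Bias in the crude rate.** With death rate λ and dropout rate d, the share seen to die by month 24 is λ/(λ+d) × (1 − e^(−24(λ+d))). The share lost alive by then is d/(λ+d) × (1 − e^(−24(λ+d))). Counting the lost as alive gives survival of 1 − dead. Dropping them gives 1 − dead/(1 − lost). The two rows for each method set the dropout of 6/45 over 24 months (d = 0.00596) or over 48 months (d = 0.00298).

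| Handling of the lost | Dropout over | Control (true 30%) | Investigational (true 55%) | Difference (true 25) |
|---|---|---|---|---|
| Counted as alive | 24 mo | 33.9% | 57.8% | 23.9 |
| Counted as alive | 48 mo | 32.0% | 56.4% | 24.4 |
| Dropped | 24 mo | 28.2% | 53.0% | 24.8 |
| Dropped | 48 mo | 29.1% | 54.0% | 24.9 |

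Each rate moves by about 1 to 4 points, and the difference by 0.1 to 1.1 points.

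**4. Standard deviation.** Under the assumed exponentials the true standard deviations of survival time are 1/0.0502 = 19.9 and 1/0.0249 = 40.1 months. The Study Duration section ends participation at the 24-month visit. Raw times confined to 0 to 24 months cannot have a standard deviation much above half that range, 12 months. The figure would reflect the cut-off more than the patients.

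**The case against.** The strongest reply is that this is a condensed article. Section 10 of the full protocol may name the primary test and the handling of losses, and describing efficacy with counts does not forbid the log-rank test stated in the same section. That stands to this extent: a reader might infer that the trial has no test matching its power claim, and the article cannot show that. What remains is not an omission. The article positively states a crude, mislabelled percentage as the efficacy result, next to a sizing paragraph built on something else.

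A second reply concerns OS and PFS. A reader might infer that these summaries ignore censoring altogether. The text does not support this: the sentence goes on to plan survival analyses with Kaplan–Meier, and a median can be read from that curve. Only the standard deviation is clearly wrong there.

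A third reply is that the bias is small. That also stands. Unequal loss, such as 9 against 3, would move the difference further (to 20.5 or 27.3 points if the lost count as alive), but the article assumes about 6 in each group and gives no ground for such a split.

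**Conclusion.** The concern holds in a limited form. The article's reported primary quantity and its sizing test do not match, and the crude percentage cannot deal with the loss that the article itself expects.

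The main consequence is for power: about 80% for the log-rank test with follow-up to month 48, against 67.5% or 59.0% for crude 24-month proportions with all 45 per arm evaluable. The bias is secondary, at about 1 to 4 points in each arm's rate and about 1 point or less in the contrast.

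These figures rest on exponential survival, non-informative dropout, and reading the loss as 6 patients in each group. They do not show a materially biased treatment comparison, nor that OS and PFS will be analysed without regard to censoring. The wrong label and the standard deviation are smaller faults in the same paragraph.

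**What to change.** Revise the analysis paragraph, and section 10 of the full protocol if it reads the same way:

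- Replace the percentage dead by the Kaplan–Meier survival rate at 24 months in each arm, and give the between-arm difference, each with a 95% confidence interval.
- State that the two-sided 0.05 log-rank test used for sizing is the primary comparison, and give its follow-up horizon. The horizon matters: with follow-up cut at 24 months and the 6/45 loss spread over 48 months, about 50 deaths are expected and Schoenfeld power is 69% to 70%.
- If a comparison at 24 months is to be primary instead, name its test and restate the power for it.
- For OS and PFS, replace the median and standard deviation by the Kaplan–Meier median with a 95% confidence interval.

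The cost is a few sentences. No new data are needed, and the sample size stays as it is if the log-rank test is confirmed with follow-up to month 48.

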### Secondary Endpoints

The secondary endpoints included the following.
To evaluate the safety of a flexible dosing schedule of [^177^Lu]Lu-PSMA-617 including up to 12 cycles and “treatment holiday” periods by Common Terminology Criteria for Adverse Events guidelines and dosimetry.To determine the overall survival, defined as the time from the date of the first cycle injection of [^177^Lu]Lu-PSMA-617 until death.To determine the PFS defined as the date of the first cycle injection of [^177^Lu]Lu-PSMA-617 to the date of first evidence of progression as defined by either radiographic progression, PSA progression, clinical progression, or death from any cause, whichever occurs first.
a.Radiographic progression is defined as the date of radiographic disease progression on SPECT/CT by visual increase in tumor volume of 30% or greater compared with baseline cycle 1 ± new sites of disease or new sites of PSMA-negative disease progression on CT (10,12) or on PSMA PET/CT as outlined in RECIP or by apparition of new PSMA-negative disease measurable on CT (13). Response assessment criteria using SPECT/CT are summarized in Table 1, and response assessment criteria on PET/CT are summarized in Table 2. See sections 6.8 and 6.9 in the study protocol in the supplemental materials.b.PSA progression is defined as the date when a 25% or greater increase in PSA and an absolute increase of 2 ng/mL or more from the nadir is documented and confirmed by a second consecutive value obtained 3 or more weeks later. Rises in PSA within the first 12 wk will be ignored in the absence of other evidence of disease progression in accordance with the Prostate Cancer Clinical Trials Working Group recommendations. Where no decline from baseline is documented, PSA progression is defined as a 25% increase from the baseline value along with an increase in absolute value of 2 ng/mL or more after 12 wk of treatment.c.Unequivocal clinical progression is defined as follows:

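### If follow-up ends 24 months after the first injection, the named summary of secondary OS (median, standard deviation) will usually fail in the investigational arm; the cause is a follow-up mismatch with the power calculation.

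*Protocol article*

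**What the plan says.** Four statements in the protocol article bear on this.

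- **Secondary Endpoints** defines OS: "To determine the overall survival, defined as the time from the date of the first cycle injection of [^177^Lu]Lu-PSMA-617 until death".
- **Statistics and Sample Size Determination** names the summary: "Descriptive analyses (median, standard deviation) will be used to determine OS and PFS". The same sentence goes on to provide for group comparisons by survival methods, with Kaplan-Meier as its example.
- **Study Duration** limits observation: "The duration of subject participation will be from the time of signing informed consent through the 24-mo postinjection visit". The Investigational Arm Timeline likewise describes safety follow-up to a total of 24 months. No section shown provides for vital-status follow-up after that.
- **Statistics and Sample Size Determination** assumes two-year survival of 30% (control) and 55% (investigational). It states that the two-sided log-rank test with 45 patients per arm "achieves 80.3% power at a 0.05 significance level to detect a hazard ratio of 0.50". The time frame for that calculation is: "The study lasts for 48 mo, of which subject accrual (entry) occurs in the first 12 mo".

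**The concern.** A median can be read from a survival curve only if the curve falls to one half while patients are still observed. Under the trial's own hypothesis, 55% of the investigational arm is alive at 24 months. If observation stops there, the median named for OS is normally out of reach in that arm, while the control median is nearly always available. The summary is more likely to be available when the strategy works less well than hoped. Better handling of censoring does not help, because a correctly computed Kaplan-Meier median is also unreached. The second named summary is no substitute: with more than half of an arm censored at one time point, the standard deviation of observed times mainly reflects the cut-off.

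Behind this lies an inconsistency. Study Duration stops at 24 months per patient, but the power calculation counts deaths up to month 48. What is at stake is how informative the secondary OS description will be, and whether the quoted power matches the follow-up that will be carried out.

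**Working it through.** **Inputs (Statistics and Sample Size Determination; Study Duration).** S(24) = 0.30 control and 0.55 investigational; 45 per arm; two-sided alpha 0.05; uniform accrual over 12 months; 48-month study; loss of around 6 per group, read here as 6/45 over 48 months; participation to 24 months. Exponential survival is assumed wherever a hazard is used.

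**1. Hazards and medians.** Hazard = -ln S(24)/24.
- Control: 1.2040/24 = 0.05017 per month; median = ln 2/0.05017 = 13.8 months.
- Investigational: 0.5978/24 = 0.02491 per month; median = ln 2/0.02491 = 27.8 months.
- Hazard ratio = 0.5978/1.2040 = 0.497, in line with the stated 0.50.

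That the investigational median lies beyond 24 months needs no exponential assumption, since 0.55 exceeds 0.50. Only the value 27.8 does.

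**2. The plan's own power.** With loss hazard g = -ln(1 - 6/45)/48 and h = hazard + g, the probability of an observed death is (hazard/h) x [1 - (exp(-36h) - exp(-48h))/(12h)]. Expected deaths are 37.8 + 27.7 = 65.5. Schoenfeld power = Phi(sqrt(65.5)/2 x |ln 0.4966| - 1.96) = Phi(4.047 x 0.700 - 1.96) = Phi(0.873) = 80.9%. It is 80.1% with HR 0.50, and a numerical log-rank calculation gives 80.6%. The stated 80.3% is reproduced. Other readings of the loss figure:

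| Loss assumed (36-48 months' follow-up) | Schoenfeld power |
|---|---|
| none | 82.6% |
| 6% per 24 months | 81.1% |
| 6/45 per 24 months | 79.1% |

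Freedman's formula gives 77.7% with 6/45 lost over 48 months and 79.6% with no loss.

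**3. Power with shorter follow-up.** With every patient cut at 24 months and no loss, deaths are 45 x 0.70 + 45 x 0.45 = 31.5 + 20.25 = 51.75. Power = Phi(3.597 x 0.700 - 1.96) = Phi(0.558) = 71.2%. With 6/45 lost by 24 months, deaths are 48.8 and power is 68.6%. The numerical log-rank calculation gives 70.5% and 67.9%. Stopping the whole study at month 36 (24 to 36 months per patient, no loss) gives 76.3%. None of these matches 80.3%.

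**4. Chance of reaching the median at a 24-month cut.** With no loss, the investigational curve reaches one half only if at least 23 of 45 patients die by 24 months: P(Bin(45, 0.45) >= 23) = 0.249. Kaplan-Meier simulation (10,000 trials, n = 45):

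| Arm and follow-up | Median reached | Upper 95% limit exists |
|---|---|---|
| Investigational, 24 months (loss 0, 6% or 13.3%) | 25-26% | under 1% |
| Control, 24 months (same losses) | over 99% | 79-84% |
| Investigational, 36-48 months (6/45 lost over 48) | 98% | 61% |
| Control, 36-48 months (6/45 lost over 48) | 100% | 100% |

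**5. A summary that survives the cut.** Restricted mean survival to 24 months = (1 - S(24))/hazard. Control: 0.70/0.05017 = 13.95 months. Investigational: 0.45/0.02491 = 18.07 months. The difference is about 4.1 months.

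**The case against.** The strongest objection is to the premise. Study Duration does not say from which injection its 24 months run. The Investigational Arm Timeline mentions the 24-month total after a phase counted from the last cycle, and plans 12-weekly assessment after cycle 12. On the six-week schedule without holidays, cycle 12 falls at 11 x 6 = 66 weeks, about 15 months. A count from the last injection would therefore carry a patient who received all 12 cycles well past 27.8 months. The power calculation itself presumes 36 to 48 months per patient, and on that follow-up the median is reached in about 98% of trials. This stands as a condition on the point. The first injection remains the natural reading, because both the primary endpoint and OS are timed from it, but the text does not settle it.

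It can also be said that an unreached median is a legitimate, reportable result, that Kaplan-Meier is already named for group comparisons, and that the article refers to section 10 of the full protocol for further analysis detail. All of that is right and limits the size of the point. It does not remove it: the article itself fixes a summary, a participation limit and a survival hypothesis that fit poorly together.

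A reader might go further and infer that the survival gain cannot be estimated, that secondary OS adds nothing to the primary endpoint, or that any benefit of cycles 7 to 12 goes unseen. The documents support none of these. The gain at 24 months is available from the primary endpoint. Time-to-event OS uses death times, which a percentage dead at 24 months does not. Without holidays, cycles 7 to 12 fall at weeks 36 to 66, which leaves about 9 to 16 months of observation after them. Late benefit is only partly lost, more so after a holiday: one of 6.1 months (the median cited in the Discussion) would move cycle 12 to about 21 months.

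**Conclusion.** The point holds, as minor to moderate, on the reading that follow-up ends 24 months after the first injection. Under the design hypothesis the investigational OS median would then be missing in about three trials in four, and a standard deviation of censored times is unsuitable in any case. The failure is confined to the descriptive summary of a secondary endpoint. The between-arm Kaplan-Meier comparison remains possible. So does the primary two-year rate: with 12-month accrual, every patient can complete 24 months by month 36.

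The follow-up mismatch behind it matters more than the median. The quoted 80.3% fits 36 to 48 months per patient and falls to about 69-71% (Schoenfeld) if observation stops at 24. A reader might conclude that the trial is underpowered. The documents do not establish that, because they do not settle which follow-up is intended; they show only that the two statements disagree. The medians, power and simulated frequencies rest on exponential survival and, where loss is included, on the reading of the loss figure given above.

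**What to change.** 1. **Reconcile Study Duration with the power calculation.** State that vital status alone, from records or by telephone, is collected for all patients to the end of the 48-month study, and that secondary OS uses it. State also from which injection the 24-month visit is counted. If follow-up does stop at 24 months, restate the log-rank power on that basis.
2. **Change the OS summary in the statistics section.** Replace the median and standard deviation with Kaplan-Meier estimates and the between-arm difference in restricted mean survival time to 24 months with its 95% CI (about 18.1 v 14.0 months under the plan's figures). Report the median with its CI where it is reached.

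Part 2 is wording only. Part 1 needs a small amendment and a consent line, within the study duration already planned and without extra patients, visits or scans. Its drawback is that deaths after 24 months will partly reflect subsequent therapies, which should be acknowledged when the longer-term OS result is interpreted.
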